## Introduction

Over the past decade, continuous advancements in diabetes technologies have helped to ease the burden of diabetes self-management for people with type 1 diabetes (T1D). Continuous glucose monitors (CGM) and automated insulin delivery (AID) systems have not only led to improved quality of life but also better glycemic outcomes and reduced incidence of hospitalizations for severe hypoglycemia and diabetic ketoacidosis (DKA) [1,2]. Given these clinical benefits, the American Diabetes Association now recommends that CGM be considered the standard of care for all people with T1D and that AID systems be recommended to people with T1D who are capable of safely using them [3].

Despite proven clinical benefits, racial inequities in the use of advanced diabetes technologies (ADTs), such as AID systems and CGMs, persist in both children and adults with diabetes [4-8]. Compared with Non-Hispanic White people with T1D, Non-Hispanic Black people with T1D have 1.5% higher glycated hemoglobin (HbA_1c_) levels on average [9] and are more than 3 times as likely to be hospitalized for hypoglycemia or DKA [10,11], yet they are half as likely to be using ADTs [12].

Factors contributing to these disparities include individual barriers like cost concerns, insertion pain, and alarm anxiety [13-16], as well as provider-level barriers such as insufficient knowledge, bias, and clinical decision-making criteria that do not align with current guidelines [17-19]. System-level barriers include insurance coverage issues and complicated processes for obtaining devices [20,21]. For example, a recent 7-year study at a large academic medical center found significantly lower rates of CGM discussions and use among Black people with T1D compared with their White counterparts, even after adjusting for various other factors [6]. In addition, a study by the T1D Exchange Quality Improvement Collaborative(T1DX-QI) highlighted the presence of implicit racial bias in approximately one-third of endocrinologists when prescribing ADTs [19].

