##### BPA Design

Using a rule-based algorithm, the EMR-based BPA will be designed to recommend ADT prescriptions for people with T1D not already using an AID system, and this would also encompass an alert for people not using CGM (and thus not using AID). The specific functionality of the BPA will be guided by the thematic analysis of the stakeholder input obtained in phase 1. The function will generate a BPA if a patient is not using an AID system and will suggest to the provider to discuss and prescribe technologies for using an AID system.

The BPA design will be led by the study organizing committee with direct involvement and support from Epic IT analysts and developers at Johns Hopkins University. Iterative feedback will be obtained from the principal investigators at each of the participating intervention centers during the prototype development. Table 3 outlines the key considerations for the design team. Throughout the design process, Norman’s user-centered design principles will be applied to ensure the BPA is intuitive, user-friendly, and meets the needs of all stakeholders [35].

**Table 3 table3:** Key considerations for best practice advisory (BPA) design team.

Consideration	Descriptions
Stakeholder input	Incorporate thematic analysis of feedback from patients, caregivers, and health care providers.
Algorithm rules	Define criteria for triggering the BPA based on patient EMR^a^ data.
Workflow integration	Ensure BPA integrates seamlessly into the provider’s workflow.
Iterative testing	Conduct iterative testing and refinement based on feedback from pilot implementations.
Setting and restrictions	Consider the setting (ambulatory, inpatient, both) and specific locations such as endocrinology clinics, primary care clinics, or health-system wide.
Location in Epic	Determine the BPA’s location in Epic, such as Windows, BPA Navigator, or Flag in Storyboard.
Active versus passive	Decide between active (windows that appear in the user’s Epic workflow) and passive (appear within assigned locations that fit into the end user’s workflow) BPAs.
Clinician action	Specify actions clinicians can take, such as placing orders or referrals.
Triggering messages	Determine language in the BPA, including potential references to practice guidelines, explain the reason for the BPA, and suggest actions to be taken.
Iterative testing	Conduct iterative testing and refinement based on feedback from pilot implementations.

^a^EMR: electronic medical record.

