##### Deployment

Following the successful completion of the validation phase at Johns Hopkins University, the BPA will be rolled out sequentially to the other intervention centers. Each institution has a CDS committee that approves new builds, and this approval process will be factored into the timeline (Figure 2). Each of the participating intervention centers has already received letters of support from institutional IT leadership; therefore, we do not anticipate any approval barriers. To ensure that each intervention center is prepared to launch the BPA at the same time, the organizing committee will recommend that the approval process for the build occur at least 90 days before the planned launch. This staged deployment strategy minimizes the risk of widespread issues and allows for iterative improvements based on real-world feedback. Once the study team has ensured that the target providers at the other 6 participating centers have received requisite training, the BPA will be moved into the Epic production environment, which will correspond to the start of the intervention phase of the study.

After deployment, we will monitor adherence to the BPA using SlicerDicer, an analytics tool integrated within Epic. This tool enables us to track the frequency of BPA activations, the acknowledgment reasons selected by clinicians, and the subsequent actions taken. SlicerDicer allows for the creation of custom reports and dashboards that visualize compliance trends over time and facilitates in-depth analysis of specific instances of noncompliance. These insights will be used to generate feedback reports for clinicians, enabling clinical leaders to compare provider compliance rates against their peers and internal benchmarks. This approach aims to encourage adherence to BPAs and foster a culture of continuous quality improvement.

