### Analysis

#### Phase 1

For survey data, Likert scale responses will be coded numerically for qualitative analysis. Descriptive statistics will be calculated to summarize the data, and differences between groups (ie, based on demographic variables) will be explored. For the structured interviews and focus groups, a thematic approach will be used to identify, analyze, and report patterns with the qualitative data. NVivo software will be used, which provides features for coding, organizing, and visualizing data [43]. Both deductive and inductive coding methodologies will be used to link similar codes to broader themes based on significant phrases, concepts, and ideas present in the transcripts [44]. Themes will be reviewed and refined through discussions among the research team to ensure consistency and reliability.

#### Phase 2

The primary outcome will evaluate the impact of the BPA intervention on patients’ progression of ADT use using a generalized linear mixed model to account for matched pairs and random center effects. The model will be adjusted for the number of encounters and other possible confounders not already matched.

The secondary outcome analyses will compare differences in ADT use between non-White and White people with T1D in the intervention and control groups. Additional secondary and exploratory outcomes will be assessed using the appropriate statistical model for the outcome adjusting for patient- and center-level confounders. Exploratory analysis assessing pediatric and adult centers separately will be performed.

In cases where ADT is not prescribed by the provider, we will explore the reasons why, and why the diabetes technology was not offered or accepted by patients. We will quantify the BPA responses as provider-led or patient-led reasons for not advancing ADT use. We will perform multivariable logistic regression analysis to evaluate whether patient characteristics (demographics, race, ethnicity, diabetes characteristics, and complications) are associated with the reasons that technologies are not offered or declined.

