## Discussion

### Principal Findings

The overarching goal of this study will be to promote the use of ADT and enhance health equity in ADT use for diabetes management in people with T1D. While previous research has illustrated the many barriers and racial disparities in ADT use, the focus of this initiative is to develop a comprehensive and evidence-based solution using HIT to address and mitigate ongoing disparities in ADT use and outcomes. We expect that clinical centers implementing the BPA will demonstrate higher rates of progression to ADT use compared with matched controlled sites, as well as a smaller gap in the use of these technologies between White and non-White patients.

In a 2-phased approach, this protocol aims to develop a BPA with input from key stakeholders, and then evaluate the effectiveness of the BPA in reducing disparities in ADT use among people with T1D. The goal of this intervention is to increase the progression of ADT use overall, while reducing health disparities and improving outcomes in all people with T1D. In addition, reasons for not prescribing ADT in response to the BPA will be collected. If successful, the build for this BPA can be disseminated to other hospital systems for implementation to improve outcomes on a larger scale.

To our knowledge, this is one of the first studies to develop and use a CDS initiative in the EMR to promote equitable discussion and prescribing of ADT in people with T1D. In addition, to increase the generalizability of our findings, a diverse sample of People with T1D will be included from multiple centers across the United States to account for geographical and systems-level (ie, state-level and insurance-based) variabilities.

Previous initiatives to improve the use of diabetes technologies in people with T1D have focused on patient-level interventions. Early initiation of CGM soon after diagnosis of T1D, and point-of-care CGM placement and education during routine diabetes care visits have led to increased uptake of CGM and improved glycemic outcomes [45-47]. A current randomized control trial deploying a diabetes navigator will determine if the help of a technology liaison can improve uptake and sustained use of ADT in people with T1D [48].

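### On its natural reading, the exploratory regression of race and ethnicity on reasons for non-use covers only non-prescribed cases, so it describes the mix of reasons and not the chance of being offered ADT or of declining it

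*Protocol article*

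**What the plan says.** The last paragraph of the Phase 2 analysis (Protocol article, Analysis) has three steps.

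- It sets the starting population: "In cases where ADT is not prescribed by the provider, we will explore the reasons why".
- It sets the coding: "We will quantify the BPA responses as provider-led or patient-led reasons for not advancing ADT use".
- It plans a multivariable logistic regression to see whether patient characteristics, race and ethnicity among them, "are associated with the reasons that technologies are not offered or declined".

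The regression sentence names no denominator and no reference category of its own.

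Three other places bear on the point.

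- Under BPA Design, the alert population is wider than the non-prescribed cases: "The function will generate a BPA if a patient is not using an AID system".
- Under Deployment, the study will "track the frequency of BPA activations, the acknowledgment reasons selected by clinicians, and the subsequent actions taken".
- Racial differences in use have a separate analysis: "The secondary outcome analyses will compare differences in ADT use between non-White and White people with T1D in the intervention and control groups".

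**The concern.** A provider-led or patient-led reason for not advancing exists only where use did not advance. A patient who was prescribed ADT has no value on that outcome, so the regression as described compares groups only within the non-prescribed cases. Its odds ratio answers this question: given that nothing was prescribed, was the reason more often the provider's in one group than in the other? Two different questions are how often each group is not offered technology, and how often each group declines once it is offered.

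The difference matters because of what the study is for. The Discussion states an aim to "promote equitable discussion and prescribing of ADT in people with T1D", and the Introduction cites "significantly lower rates of CGM discussions and use among Black people with T1D". The secondary analysis measures use, which combines offering and accepting. The reasons regression is the only described analysis that separates provider non-offer from patient decline by race and ethnicity. A null or reversed provider-led odds ratio could be taken to mean that the remaining gap is patient choice when non-offer is in fact higher in the target group.

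**Working it through.** **Inputs.** The protocol gives no offer rate, decline rate or other figure for this regression, so there is no figure to reproduce. All rates below are assumptions. Each alerted patient is given one of three outcomes:

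- not offered (provider-led), probability q
- offered but declined (patient-led), probability (1 − q)d, where d is the chance of declining if offered
- prescribed, probability (1 − q)(1 − d)

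**Formula.** Among non-prescribed patients, the odds of provider-led versus patient-led are q / [(1 − q)d]. The ratio of these odds, minority to White, is

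conditional OR = OR of not offered × (d in White patients / d in minority patients).

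The conditional OR therefore equals the offering OR only when d is the same in both groups.

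**Offering disparity assumed.** With q = 20% in White and 30% in minority patients, the true OR is (0.30/0.70)/(0.20/0.80) = 1.71. The difference is 10 points and the risk ratio 1.50. These values are the same in cases A to C.

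| Case | q, White / minority | d, White / minority | Patient-led, White / minority | Provider-led share of non-prescribed, White / minority | True OR | Conditional OR |
|---|---|---|---|---|---|---|
| A. Equal decline | 20% / 30% | 50% / 50% | 40% / 35% | 33% / 46% | 1.71 | (0.30/0.35)/(0.20/0.40) = 1.71 |
| B. Hidden | 20% / 30% | 37.5% / 64.3% | 30% / 45% | 40% / 40% | 1.71 | (0.30/0.45)/(0.20/0.30) = 1.00 |
| C. Reversed | 20% / 30% | 25% / 64.3% | 20% / 45% | 50% / 40% | 1.71 | (0.30/0.45)/(0.20/0.20) = 0.67 |
| D. Created | 20% / 20% | 50% / 25% | 40% / 20% | 33% / 50% | 1.00 | (0.20/0.20)/(0.20/0.40) = 2.00 |

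Case A gives 1.71 with d at 30% or 70% in both groups as well.

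**How different must declining be to hide the disparity fully?** Setting the conditional OR to 1 gives d(minority) = 1.71 × d(White). For a White rate of 20%, 30%, 40% or 50%, the minority rate must be 34%, 51%, 69% or 86%. At a White rate of 60% it would have to exceed 100%, so the disparity could then be weakened but not fully hidden.

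**The patient-led side.** In a binary contrast, the patient-led OR is the reciprocal of the provider-led OR. In case A it is (0.35/0.30)/(0.40/0.20) = 0.58, although half of those offered decline in both groups and the OR for declining if offered is 1.00. One contrast cannot answer both the not-offered and the declined question.

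**Why the denominator for decline also needs care.** In case A, modelling decline over all alerted patients gives 40% versus 35%, an OR of (0.35/0.65)/(0.40/0.60) = 0.81. Minority patients would seem less inclined to decline only because fewer were offered. Decline has to be modelled among those offered.

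**The case against.** The strongest reply is that the paragraph sets out to explore reasons, and reasons exist only among non-prescribed cases, so a model of their mix answers the question as worded. This stands in part. Nowhere does the protocol say that the regression tests whether minority patients are offered technology less often, and equal offering is not a stated null hypothesis. The analysis is exploratory in character.

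Second, restriction to non-prescribed cases is an inference. The regression sentence names no denominator, and a model of not offered against all other outcomes is not excluded. That also stands, although the opening of the paragraph and the two-way coding make the restricted reading the natural one.

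Third, the distortion is conditional, and exact cancellation as in case B needs a particular ratio of decline rates. This is correct. A reader might infer that the regression misleads whenever prescribing differs by race. Case A shows otherwise: prescribing is 40% versus 35%, yet the provider-led OR is exact. The protocol does not assume equal declining, however. Its Introduction lists individual barriers such as cost, pain on insertion and alarm anxiety among the contributors to the disparities. Any ratio of decline rates other than 1 shifts the odds ratio by that ratio.

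A reader might also infer that the trial's assessment of racial disparity is compromised. The documents do not support this. The disparity in ADT use has its own secondary analysis, and neither that nor the primary model depends on the reasons regression.

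**Conclusion.** The point holds as a limit on what an exploratory analysis can show, with a better method at hand. On the natural reading, the regression describes how reasons divide among non-prescribed cases. It does not estimate the chance of being offered ADT or of declining it when offered. For one assumed offering disparity (20% versus 30%, OR 1.71), the provider-led odds ratio is 1.71, 1.00 or 0.67 depending only on decline rates, and it can be 2.00 when offering is equal. With equal declining the provider-led odds ratio is right, but the patient-led one is still wrong as a measure of willingness to accept (0.58 instead of 1.00).

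This rests on the inferred denominator, on one three-way outcome per patient, and on assumed rates. The arithmetic shows what is possible, not what is likely at these centers. It should be changed because it is the only described analysis that separates non-offer from decline by race and ethnicity.

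**What to change.** State the denominator of the reasons regression and put two models in its place:

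1. Not offered (provider-led), yes or no, among all eligible intervention-center patients for whom the BPA fired.
2. Declined (patient-led), yes or no, among those offered, that is, those prescribed plus those with a patient-led decline.

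Define one patient-level outcome over the 12 months, or account for repeat alerts. Table 1 leaves the alert frequency open, so one patient may have a refusal and a later prescription. Report adjusted probabilities by race and ethnicity from both models. Keep the provider-led versus patient-led split among non-prescribed cases as description only, and say that it describes the mix of reasons.

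The cost is a second model, a rule for repeat alerts, and linkage of alert firings to prescriptions. Deployment says that activations, acknowledgment reasons and subsequent actions are already to be tracked, so no new data item appears to be needed.

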### Control Group

Matched control people with T1D will be selected from the pool of nonintervention clinical centers sharing EMR data with the T1DX-QI coordinating center with over 80,000 people with T1D data available in the database.

To accurately match people with T1D between the intervention and control groups, we will identify and include a comprehensive set of covariates that may influence the likelihood of receiving the BPA. These covariates will include both patient-level and clinical center-level characteristics. Patient-level characteristics will include demographics (age, sex, race, and ethnicity), socioeconomic status (insurance type and zip code–based income), and clinical characteristics (duration of diabetes, comorbidities, HbA_1c_ levels, etc). Clinical center-level characteristics will include clinic size and resources (number of people with T1D seen annually, number and type of clinical full-time equivalents, geographic location, patient population demographics, and historical usage rates of CGMs and AID systems. Intervention and control groups will be matched using the propensity score method.

Before propensity score matching, any missing baseline covariate data will be imputed using predictive modeling techniques. Multiple imputation by chained equations will be used to generate multiple complete datasets, which will then be averaged to create a single dataset for the matching process. This approach ensures that the imputed values are based on observed data, maintaining the integrity and representativeness of the dataset.

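### Alert responses are classed as provider-led or patient-led, with no class for the system-level barriers that the protocol names, so such reasons may be misattributed in the exploratory reasons regression

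*Protocol article*

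**What the plan says.** The Introduction of the protocol article sorts the causes of the disparity into three levels. At patient level it lists "individual barriers like cost concerns, insertion pain, and alarm anxiety". It then lists provider-level barriers, and separately: "System-level barriers include insurance coverage issues and complicated processes for obtaining devices".

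Analysis, Phase 2, opens its last paragraph with "In cases where ADT is not prescribed by the provider, we will explore the reasons why". It goes on to fix the classification: "We will quantify the BPA responses as provider-led or patient-led reasons for not advancing ADT use". A multivariable logistic regression will then examine whether "patient characteristics (demographics, race, ethnicity, diabetes characteristics, and complications) are associated with the reasons that technologies are not offered or declined".

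Other relevant places:
- Control Group lists "socioeconomic status (insurance type and zip code–based income" among the patient-level matching covariates, as an item separate from demographics.
- Deployment says that the acknowledgment reasons chosen by clinicians will be tracked, but does not list the options.
- BPA Design leaves the detailed function of the alert to the Phase 1 findings.

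No section says how a coverage or procurement reason will be classified.

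**The concern.** The coding rule has two classes, whereas the protocol's own account of the problem has three levels. A clinician who closes the alert without prescribing because coverage is expected to be refused, or because the procurement route is blocked, fits the third level. Under the rule as written, that response must be filed on one of the two sides or left unclassified.

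This is the only Phase 2 analysis in the article that asks why the alert did not lead to ADT, and it relates the answers to race and ethnicity in a trial about racial inequity. Coverage reasons filed as patient-led would read as patients declining technology. Filed as provider-led, they would read as provider choice. Each reading suggests a different remedy, and neither addresses coverage. If no system option exists when the alert goes live, the information may not be recoverable afterwards.

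**Working it through.** **Figure to reproduce.** None. The plan states no number for the reasons analysis, and the sample size calculation is not an input to this point.

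**The passages side by side.**

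| Level in the Introduction | Class in Analysis, Phase 2 |
|---|---|
| Individual | Patient-led |
| Provider | Provider-led |
| System (coverage, obtaining devices) | None stated |

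**Could it matter numerically?** The inputs below are assumptions, because the documents give no shares.

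- s is the share of system reasons among non-advanced cases: s1 in non-Hispanic Black and Hispanic patients, s0 in White patients.
- The remaining reasons split 50:50 between patient-led and provider-led in both groups, so the true odds ratio (OR) is 1.00.
- f is the fraction of system reasons filed as patient-led, the same in both groups.
- There is no adjustment for insurance or income.

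The recorded patient-led share is 0.5(1 − s) + f·s. The odds are therefore [1 + s(2f − 1)] / [1 − s(2f − 1)], and the OR is the ratio of the two groups' odds.

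With all system reasons filed as patient-led (f = 1), the odds are (1 + s)/(1 − s). For s1 = 0.30 and s0 = 0.15: (1.30/0.70) / (1.15/0.85) = 1.857/1.353 = 1.37. With all filed as provider-led (f = 0), the OR is the reciprocal, 0.73.

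| s1 | s0 | OR, all filed patient-led | OR, split evenly | OR, all filed provider-led |
|---|---|---|---|---|
| 10% | 10% | 1.00 | 1.00 | 1.00 |
| 20% | 10% | 1.23 | 1.00 | 0.81 |
| 30% | 15% | 1.37 | 1.00 | 0.73 |
| 30% | 10% | 1.52 | 1.00 | 0.66 |
| 40% | 10% | 1.91 | 1.00 | 0.52 |

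**Partial filing.** For 30% and 15% with f = 0.7, the patient-led shares are 0.35 + 0.21 = 0.56 and 0.425 + 0.105 = 0.53. The OR is (0.56/0.44) / (0.53/0.47) = 1.273/1.128 = 1.13.

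**Direction.** Exchanging s1 and s0 inverts every OR. The sign thus depends both on where system reasons are filed and on which group has more of them.

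**Left unclassified.** If system reasons are dropped, the OR in this set-up stays at 1.00, but the analysis then says nothing about coverage.

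**The case against.** The strongest reply is that the two labels record who stopped the advance, not the root cause. The same paragraph speaks of technology not offered or declined, and the labels match that split. On this reading, a provider who withholds an offer because refusal is expected is provider-led, and a patient who declines over cost is patient-led; the Introduction itself lists cost concerns as an individual barrier. This reading is coherent. It does not remove the problem, because it still merges coverage-driven non-prescribing with provider choice or patient refusal, and no other section separates them.

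Several other points stand and limit the finding:

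- A reader might infer that only two classes will ever be used and that coverage failures will in fact be booked as refusal or provider choice. The text says neither; their handling is not stated, and the acknowledgment options are still open.
- A reader might also infer that the outcome of the regression is the two-way label. The article says only that characteristics will be related to the reasons, and one model per reason would fit that wording.
- The analysis covers cases where ADT was not prescribed, so an insurer's denial after a prescription may fall outside it.
- It is arguable whether insurance is omitted. The preceding paragraph adjusts additional secondary and exploratory outcomes for patient-level confounders, which could include it. The list for this regression does not name it, and adjustment would not restore a missing category.
- Phase 1 also collects reasons for not prescribing, by qualitative methods.

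**Conclusion.** The point holds in a limited form. The plan states a two-way classification that does not fit its own three-level account of the barriers, so system-level reasons may be misattributed in the exploratory reasons regression.

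Bias in the race association there requires two conditions: system reasons must differ in frequency by race, and they must be filed unevenly between the two classes. The documents give no figures for either, so the size is unknown. The odds ratios above show only what assumed shares, a 50:50 remainder, equal filing in both groups and no adjustment would produce.

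The stronger reading, that the trial's race analysis is distorted, is not supported. The primary model of ADT progression and the secondary comparison of non-White and White ADT use do not use these reasons.

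This is a cheap improvement to one exploratory analysis.

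**What to change.** 1. Before go-live, add a system-led acknowledgment category (coverage, authorization, procurement) to the provider-led and patient-led ones, and state in Analysis, Phase 2, that responses are quantified in three classes.
2. Analyse the reasons with a multinomial model, or with one logistic model per reason against all others.
3. Name insurance type and zip code-based income, already planned as matching covariates under Control Group, among the predictors, and show the race association with and without them.

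The cost is one more response option in an alert whose content is still being designed, plus a few sentences of analysis text. The downside is fewer cases per category and wider intervals.
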